#### 2.6.4. Blinding Assessment

As described above, the patients will be asked which group they think they belong to after the final session to calculate the BI [16].

### 2.7. Statistical Analysis

Categorical variables will be presented with frequencies and percentage and analyzed by *χ*
^2^ test or Fisher's exact test for demographic information and adverse events. Continuous variables will be presented with mean ± standard deviation and analyzed by two-sample *t*-test or Mann-Whitney *U*-test for demographic information and effectiveness outcomes, depending on the normality of the baseline distribution. If necessary, efficacy data will be evaluated with analysis of covariance (ANCOVA) with covariates of recruiting center and any demographic information, such as gender.

Full analysis set (FAS) (defined as the data set of the participants who receive 7 or more EA or SA sessions and provide the primary outcome at least once) will be primarily used for the effectiveness assessment. Per-protocol (PP) analysis (defined as the data set of the participants who complete every 10 EA or SA session) will be subordinately adopted. Missing data will be imputed by the last observation carried forward method. For the safety assessment, safety set analysis will be performed with the data obtained from all of the participants who receive at least one EA or SA session.

Finally, for the BI assessment, the distribution of actual allocation and participant's responses (EA group, SA group, or DO NOT KNOW) will be presented with 2 × 3 cross tabulation along with the index calculation.

IBM SPSS Statistics for Windows (Version 21.0. IBM Corp. Released 2012. Armonk, NY, USA) will be used, with 0.05 significance levels by a 2-sided test.

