## 1. Background

Urinary incontinence (UI) is defined as involuntary loss of urine [1], with reduced ability either to be aware of bladder signals before leakage or to take notice of eventual leakage or both [2]. The damaged neurological lesions in the brain of stroke survivors lead to loss of control of detrusor function, which is the reason that poststroke patients often experience UI [3, 4].

A previous study reviewed 9 papers from European countries, USA, and Japan and reported that the UI prevalence in stroke patients was estimated by 32% to 79% at admission and 25% to 28% at discharge [4]. A study suggested that the prevalence of poststroke urinary incontinence (PSUI) might be as high as 45.6% in Korea, which is higher than that of UI [5].

Urinary dysfunction generally affects the quality of life in stroke survivors [6], but the development of UI following a stroke is also a predictor of future functional recovery after acute stroke [7], with a strong association with both increased mortality rates and poor functional outcomes [8]. As a result, clinicians and researchers have been highly interested in the management or treatment of poststroke UI.

Recommended treatments for poststroke UI include bladder retraining, timed or prompted voiding, intermittent catheterization, the use of anticholinergic medications, and environmental and lifestyle support, none of which have sufficient evidence of efficacy, according to a systematic review [8]. Acupuncture therapies have been also explored for the management of UI after stroke in China. For example, stroke survivors who received acupuncture showed lower rates of UI than those who received no treatment or usual care, even though the quality of studies was questionable [8]. Another review implied that acupuncture or acupressure therapies exhibited favorable effects on UI patients with overactive bladder symptoms and suggested that a more qualified randomized controlled trial (RCT) should be implemented [10]. A Chinese study conducted a multicenter RCT and reported the positive clinical efficacy of electroacupuncture (EA) for apoplectic UI compared with indwelling catheterization [11].

However, there have been no RCTs to determine whether EA is effective for UI in poststroke patients compared with a sham comparator. This pilot study is aimed at evaluating the effectiveness and safety of EA therapy for poststroke patients with UI, to explore suitable conditions for a future full-scale RCT.

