#### 2.2.4. Sample Size Calculation

Because there is no preceding study to evaluate the effectiveness of EA for PSUI using the Total Urgency and Frequency Score (TUFS), with a control of any sham devices, we reviewed a statistical study on the appropriate group size for a pilot study. One study suggested that at least 12 participants should be recruited in each group to conduct a pilot trial [14], and another suggested that an increase in size from 12 to 18 or 24 narrowed the confidence interval [15]. Accordingly, we decided that 18 participants per group would be adequate. Therefore, with anticipated dropout rates of 10%, totally 40 participants (20 per group) will be randomized and allocated each EA or sham acupuncture (SA) group.

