### 2.3. Randomization and Group Allocation

An independent statistician will generate a singular sequence of random numbers using the R program (R Foundation for Statistical Computing, Vienna, Austria. http://www.r-project.org/) for the entire study. The participants will be given a unique screening number by the order of signing of informed consent, and they will be randomly allocated to either the EA or SA group.

After requesting group allocation, the investigators will receive an email or text message from the statistician including the group assignments for the patients. The allocation ratio is 1 : 1 (20 in the EA group or SA group, resp.).

The electronic file with random sequence and allocation information can be accessed by the independent statistician until the trial cessation or closeout.

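### The only between-group inference named for adverse events is a χ²/Fisher test at 0.05 in at most 20 versus 20 patients; it has little power for moderate excess harm, and intervals would tell the next trial more

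*Protocol article*

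**What the plan says.** The Background (section 1) puts safety beside effectiveness: "This pilot study is aimed at evaluating the effectiveness and safety of EA therapy for poststroke patients with UI". It then adds that the pilot should explore conditions for a later full-scale trial.

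Section 2.7 gives the method for harms: "Categorical variables will be presented with frequencies and percentage and analyzed by" χ² "test or Fisher's exact test for demographic information and adverse events". The level is set for all tests together: SPSS "will be used, with 0.05 significance levels by a 2-sided test". The safety set is everyone who receives at least one session of either treatment.

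On numbers, section 2.3 states "The allocation ratio is 1 : 1 (20 in the EA group or SA group, resp". Section 2.2.4 bases the size on pilot rules of thumb, one of them being that "an increase in size from 12 to 18 or 24 narrowed the confidence interval". It does not use a power calculation.

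The test is not the whole of the safety plan. Section 2.6.3 has adverse events checked after every session and rated for severity, seriousness and causality. The Discussion says that safety will be assessed through adverse event reporting, and it leaves confirmation of safety to a full-scale trial.

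**The concern.** The group size was argued partly from confidence interval width, but the comparison of harms is made by a significance test for which the trial was never sized. With 20 patients per arm, such a test returns p > 0.05 for most moderate excesses of adverse events. That result cannot separate an absence of extra harm from too few patients to see it.

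An excess is plausible. Under sections 2.5.1 and 2.5.2, the electroacupuncture needles penetrate 10–15 mm, de qi is elicited and current is delivered. The sham needles do not penetrate.

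What is at stake is the information passed on. The Discussion says the results will shape a full-scale trial. The planners of that trial need to know how large an excess of adverse events the pilot data still allow, and a p-value does not tell them.

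**Working it through.** **Inputs from the protocol.** Two-sided level 0.05 and χ² or Fisher's exact test (section 2.7). 20 randomised per arm (section 2.3). Safety set of all with at least one session, so at most 20 per arm (section 2.7).

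**The plan's own figure.** Section 2.2.4 says "we decided that 18 participants per group would be adequate" and "with anticipated dropout rates of 10%, totally 40 participants (20 per group) will be randomized". 18 / (1 − 0.10) = 20 per group, 40 in total. This reproduces. It is not a power figure, and none is given for adverse events.

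**Assumptions.** The protocol states no adverse event rates, so a range is shown. The χ² figures are for the uncorrected Pearson statistic.

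**Rejection region, 20 versus 20.** Smallest number of electroacupuncture patients with an event that gives p ≤ 0.05:

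| Sham events | Fisher | χ² |
|---|---|---|
| 0 | 5 | 4 |
| 1 | 7 | 6 |
| 2 | 9 | 8 |

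**Power.** This is the sum of the binomial probabilities of all 21 × 21 outcomes with p ≤ 0.05. The case of 0% versus 20% can be checked by hand, because sham events are then always 0. Fisher power is P(X ≥ 5) and χ² power is P(X ≥ 4), with X ~ Bin(20, 0.20), giving 0.370 and 0.589.

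| Assumed sham vs EA | Power, Fisher | Power, χ² | Missed, Fisher | Missed, χ² |
|---|---|---|---|---|
| 0% vs 10% | 4% | 13% | 96% | 87% |
| 0% vs 20% | 37% | 59% | 63% | 41% |
| 5% vs 20% | 17% | 29% | 83% | 71% |
| 5% vs 25% | 30% | 44% | 70% | 56% |
| 10% vs 30% | 24% | 36% | 76% | 64% |
| 5% vs 50% | 89% | 94% | 11% | 6% |

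Fisher reaches 80% power only at about 5% versus 44.5%, or 10% versus 53%. With 18 per arm, power for 5% versus 20% falls to 13% (Fisher) and 25% (χ²). By the pooled formula, 80% power for 5% versus 20% would need 76 per arm.

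**Disagreement between the two permitted tests, 4/20 versus 0/20.**
- Fisher: p = 2 × C(20,4) / C(40,4) = 2 × 4,845 / 91,390 = 0.106.
- Uncorrected χ²: 40 × (4 × 20 − 16 × 0)² / (20 × 20 × 4 × 36) = 256,000 / 57,600 = 4.44, p = 0.035.

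**What intervals would show.**
- 0/20 in an arm: exact two-sided 95% upper limit = 1 − 0.025^(1/20) = 16.8%.
- 3/20 versus 1/20: Fisher p = 0.60. The Wilson limits are 5.2% to 36.0% and 0.9% to 23.6%. The Newcombe interval for the difference of 10 points is
  - lower: 0.10 − √[(0.15 − 0.052)² + (0.236 − 0.05)²] = −0.11
  - upper: 0.10 + √[(0.360 − 0.15)² + (0.05 − 0.009)²] = +0.31
- 4/20 versus 1/20: Fisher p = 0.34, Newcombe interval about −7 to +37 points.

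**The case against.** The case for the plan has four parts.

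**The test is not the safety conclusion.** A reader might infer that the p-value alone answers the safety question. The documents do not support that. Frequencies and percentages are planned in the same sentence as the test, and section 2.6.3 adds event-by-event ratings. This stands, and the point is limited to the between-group inference.

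**No misuse is planned.** A reader might also infer that p > 0.05 will be reported as evidence of safety. No section says so, and the Discussion reserves confirmation for a full-scale trial. This stands too. The risk lies in how a results table may be read, not in a stated rule.

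**Intervals may be in the full protocol or analysis plan.** A condensed article often leaves out such detail, so the absence of an interval is not itself a fault. What can be criticised is the method the article does fix: a 0.05 test for harms in a sample sized on other grounds. The percentages describe each arm but do not show how large a difference remains compatible with the data.

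**The missed harms rest on assumed rates, and χ² does better.** Both are correct. The protocol defines no relevant harm, and very large differences would be detected, so it cannot be said that the test misses most relevant harms. Fisher is the likelier choice when events are few: at 4/20 versus 0/20 the expected count in each event cell is 4 × 20 / 40 = 2. That makes disagreement between the tests less of a practical problem, but it also puts the trial on the lower power figures.

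**Conclusion.** The point holds in a limited form. For a stated aim, the only between-group inference named is a test with about 17% (Fisher) or 29% (uncorrected χ²) power to detect a rise in adverse events from 5% to 20%, and 37% or 59% for 0% versus 20%. These figures assume independent binomial counts, 20 treated patients per arm and rates that the protocol does not supply. The interval results depend only on the illustrative counts.

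No stated figure is wrong and no sections conflict. Data collection, the safety set and the planned counts are unaffected. The weakness is that a non-significant result would say little about harm, while the same counts could show directly what excess remains possible. Severity is minor, and this is a cheap improvement.

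**What to change.** In section 2.7, separate adverse events from the sentence on χ² and Fisher tests, and for the safety set state:

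- the number and proportion of patients with at least one adverse event in each arm, with exact 95% confidence intervals, including the exact upper limit where an arm has no events;
- the EA-minus-SA risk difference with a 95% interval, for example Newcombe;
- that the adverse event test is dropped, or kept and labelled exploratory;
- that a non-significant difference will not be taken as evidence of safety.

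The cost is two or three sentences, with no new data, visits or patients, because the intervals come from counts already planned. The downside is that the intervals will be wide and the safety statement less reassuring than a bare report of no significant difference.

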#### 2.6.1. Primary Outcome

The change in TUFS will be primarily evaluated. PPIUS is a self-rated diary reporting time points, frequency of urination, and the intensity of urine urgency in 24 hours. The patient's perception of intensity is scored from 0 (no urgency) to 4 (urgency incontinence). TUFS is calculated using the sum of the PPIUS scores. This scale has been validated to assess the severity of overactive bladder and Lower Urinary Tract Symptoms, combining the symptoms of urgent and frequent urination [20]. The patient will be asked to report the scale for 24 hours at baseline and at the end of the trial, respectively.

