## 3. Discussion

This study protocol is intended to conduct a pilot multicentered, randomized, parallel, sham-controlled trial, evaluating the effectiveness and safety of EA, compared with SA, for PSUI patients. The primary effectiveness will be measured by a patient-reported scale, TUFS, with other outcomes, namely, ICIQ-UI-SF, K-IPSS, and LUTS Outcome Score. The safety will be analyzed with adverse events reporting.

According to a review study on acupuncture for voiding disorders after stroke, CV4, SP6, CV3, and CV6 are the 4 acupoints that have been most used in 16 clinical studies [26]. These acupoints are known to control the kidney or body fluid and can possibly manage bladder problems, according to the literature on Korean traditional medicine [18].

Park sham is a placebo acupuncture that was developed to make patients indistinguishable from those who receive genuine needling [27]. With use of a specially developed guide tube, patients cannot observe the needle penetrating through the skin. We will use this guide tube to blind participants, even in the actual EA group. The validation test for SA has already been performed [28].

We designed this trial as a pilot study because no preceding study exists. With the results, we expect to explore more adequate trial settings and calculate statistically powered sample sizes for a full-scale clinical trial to confirm the effectiveness and safety of EA therapies for UI in stroke survivors.

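### The t-test/Mann-Whitney choice is keyed to baseline normality although the primary variable is the change in TUFS, and the optional ANCOVA leaves the primary model unfixed and does not name baseline TUFS

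*Protocol article*

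**What the plan says.** Section 2.6.1 of the Protocol article defines the primary outcome: "The change in TUFS will be primarily evaluated". TUFS is measured twice: "The patient will be asked to report the scale for 24 hours at baseline and at the end of the trial, respectively". Table 1 places these measurements at V2 (day 0) and V13 (closeout).

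Section 2.7 names the two-sample t-test or the Mann-Whitney U-test for continuous variables, "for demographic information and effectiveness outcomes", with the choice made "depending on the normality of the baseline distribution". It gives no normality test or threshold. It then adds: "If necessary, efficacy data will be evaluated with analysis of covariance (ANCOVA) with covariates of recruiting center and any demographic information, such as gender". It does not say when this is necessary, whether the ANCOVA replaces or supplements the first test, or which demographics qualify.

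The same section presents continuous variables as mean and standard deviation and tests at a two-sided 0.05 level. Section 2.2.4 plans 18 evaluable patients per group. The Discussion expects the results to help "calculate statistically powered sample sizes for a full-scale clinical trial".

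**The concern.** Three features of this text cause difficulty.

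1. **The rule checks the wrong distribution.** The t-test's normality assumption concerns the variable being compared, here the change in TUFS within arms. Baseline TUFS can be skewed while the change is well behaved, or the reverse. One sentence covers demographics and effectiveness outcomes together. A baseline criterion suits the demographics but not the outcomes.
2. **The primary model is not fixed.** A t-test, a Mann-Whitney test and an ANCOVA with an open covariate list are all compatible with the text, and nothing states which result is primary.
3. **Baseline TUFS is not a named covariate.** It is the natural adjustment variable for a change from baseline, and the schedule already collects it in every patient.

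At stake are some room to choose the reported analysis after seeing the data, and precision in a trial of about 36 evaluable patients whose estimates are meant to inform a larger one.

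**Working it through.** **The plan's own figure.** 18 per group with 10% dropout: 18/(1 − 0.10) = 20 per group, 40 in total. This reproduces. The article states no effect size, SD or power, so there is no power figure to check.

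**Inputs.** From the article: 18 evaluable per arm, two-sided alpha 0.05, one baseline and one final TUFS. Assumed, because the article does not give them: equal SD at both visits (set to 1), a true difference of 0.8 score SD, and rho from 0.3 to 0.8.

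**Precision.**
- SD of the change = √(2(1 − rho)).
- Residual SD after adjusting the final score for baseline = √(1 − rho²).
- Variance ratio, ANCOVA to change score = (1 − rho²)/(2(1 − rho)) = (1 + rho)/2.
- Power (normal approximation) = Φ(0.8/(SD × √(2/18)) − 1.96).

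Example at rho = 0.5. Change score: SD 1, 0.8/0.333 = 2.40, Φ(0.44) = 67%. ANCOVA: SD 0.866, 0.8/0.289 = 2.77, Φ(0.81) = 79%.

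| rho | Variance ratio | Power, ANCOVA | Power, change-score t-test | Difference detectable at 80% power, ANCOVA vs change (score SD) |
|---|---|---|---|---|
| 0.3 | 0.65 | 71% | 53% | 0.891 vs 1.105 |
| 0.5 | 0.75 | 79% | 67% | 0.809 vs 0.934 |
| 0.7 | 0.85 | 92% | 87% | 0.667 vs 0.723 |
| 0.8 | 0.90 | 98% | 97% | 0.560 vs 0.591 |

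**Simulation of the stated rule.** 4,000 trials per setting, 18 per arm, rho 0.3, 0.5 and 0.7, normal or log-normal scores. The test was selected by Shapiro-Wilk at 0.05 on pooled baseline TUFS. Shapiro-Wilk is an assumption, since the article names no test.

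- *Wrong distribution.* A check on baseline and a check on the within-arm residuals of the change pointed to different tests in about 9–10% of trials with normal scores and 48–55% with log-normal scores. In the log-normal case baseline was called non-normal in about 91% of trials.
- *Type I error.* The rule followed literally gave 0.043 to 0.054. The Monte Carlo standard error is √(0.05 × 0.95/4000) = 0.003, so this is close to nominal. If the analyst may report either the selected test or an ANCOVA on centre and gender, it was 0.061 to 0.066.
- *Power at 0.8 score SD, stated rule vs baseline-adjusted ANCOVA.* Normal scores: 51% vs 68%, 64% vs 75% and 85% vs 89% at rho 0.3, 0.5 and 0.7. Log-normal scores: 62% vs 71%, 75% vs 77% and 91% vs 88%. In the last setting the rank test, which the rule usually selects there, is slightly better.

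**The case against.** The best defence is that this is an unpowered pilot and the consequences are mild. Much of that stands.

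- A reader might infer that a data-driven choice of test inflates the false-positive rate. The baseline switch does not do so materially, because the treatment effect cannot steer baseline data. What looseness there is comes from the undefined trigger and open covariate list of the ANCOVA. The simulated inflation is modest, though it covers one optional model and the text permits others.
- A reader might infer that choosing the rank test would leave the pilot without means or SDs for planning. Section 2.7 presents mean and standard deviation whichever test is used, so this does not hold.
- A reader might infer that p < 0.05 decides whether to proceed to a full-scale trial. The article sets no such rule; it states a significance level only.
- A reader might infer that baseline adjustment is always much more powerful. The article gives neither rho nor the distribution of TUFS. The gain falls to a few points at rho 0.7 to 0.8 and can reverse slightly with skewed scores.

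ANCOVA might also be meant as supplementary, but the text does not say so. Nor can the matter be left to an unseen analysis plan, since the article itself states the baseline criterion and the conditional clause. The defence limits the size of the problem; it does not make the rule sound.

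**Conclusion.** The point holds in a limited form and is a should-fix. Section 2.7 keys the test for the primary outcome to a distribution other than that of the variable tested. It leaves the primary model open and does not name baseline TUFS as a covariate.

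The error-rate consequence is small: near 0.05 under the literal rule, and about 0.06 with one optional ANCOVA. The precision consequence ranges from a 35% lower variance with baseline adjustment at rho 0.3 (1 − 0.65) to 10% lower at rho 0.8 (1 − 0.90). The power gain is correspondingly large at low rho and negligible at 0.8. These figures rest on an assumed rho, equal SDs at both visits and an assumed 0.8 SD difference. The tabulated powers also assume normal scores. The sample size of 40 is unaffected.

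**What to change.** In section 2.7, name one primary analysis in advance: ANCOVA of end-of-trial (V13) TUFS on arm, baseline (V2) TUFS and centre, reported as the adjusted mean difference with its 95% confidence interval and the residual SD. Judge assumptions on the model residuals, not on baseline, and pre-specify a rank-based sensitivity analysis in case they are skewed. Delete the baseline-normality switch for effectiveness outcomes and the conditional ANCOVA clause with its open demographic list.

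The cost is wording only: no extra patients, visits or measurements. The gain is one primary result, usually better precision, and a residual SD that can be used directly in sizing the full-scale trial.

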#### 2.2.3. Dropout Criteria

Participants will be dropped out when any one of the following criteria apply: (a) any of the aforementioned exclusion criteria is found after the patient screens in; (b) patients or their legal representatives withdraw consent or want to suspend participation; (c) investigators lose contact with the participant; (d) investigators or patients violate the trial protocol; (e) patients have serious or permanent injury from the trial; (f) patients take any drugs that can affect the results of the trial without direction by the investigators during the trial; or (g) patients have other sufficient reasons to interrupt the trial progress, as determined by investigators' clinical experience.

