#### 2.5.2. Sham Group

The control group will receive Park sham therapy using the following procedures. (a) The patient will be placed in lateral decubitus position. (b) The practitioners will install the same guide tubes at the same acupoints as in the EA group. (c) Nonpenetrating SA is implemented at each acupoint through the guide tubes. (d) Electrical stimulation is applied for 20 minutes at middle frequency (30 Hz), even though the stimulation is not delivered because the needles have not penetrated the skin.

The treatment session for both groups will be repeated 10 times for 18 days (the visit window is ±3 days). The patients will not take more than one session per day. Acupuncture practitioners with at least 1 year of clinical experience will be involved in the procedures. The practitioners will only explain how many needles will be used, where they are going to place the needles, and how long the needles will remain in place during the session.

The acupoints were selected based on a literature review of Korean acupuncture theories and expert consensus reached after discussion. The selected acupoints are usually used for bladder and genital disorders, including the general symptom of residual urine [18].

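### The primary effectiveness set requires 7 of 10 sessions, so the main comparison is selected on post-randomisation adherence and can be biased in either direction

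*Protocol article*

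**What the plan says.** Section 2.7 names three analysis sets.

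- The full analysis set (FAS) is "the participants who receive 7 or more EA or SA sessions and provide the primary outcome at least once". It "will be primarily used for the effectiveness assessment".
- The per-protocol set, used as a subordinate analysis, is "the data set of the participants who complete every 10 EA or SA session".
- The safety set is "all of the participants who receive at least one EA or SA session" and serves the safety assessment only.

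On gaps in the data the same section says: "Missing data will be imputed by the last observation carried forward method".

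Section 2.5.2 gives the planned exposure: "The treatment session for both groups will be repeated 10 times for 18 days". Table 1 places allocation at V2, the ten sessions at V3 to V12 and closeout at V13. TUFS, the primary outcome, is assessed after screening only at V2 and V13 (section 2.6.1 and Table 1).

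Section 2.2.3 lists reasons for dropping a participant. They include "investigators or patients violate the trial protocol" and "any of the aforementioned exclusion criteria is found after the patient screens in", as well as withdrawal, trial injury, undirected drug use and investigator judgement.

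**The concern.** A full analysis set should stay as close as possible to all randomised patients, because randomisation is what makes the arms comparable. A threshold of 7 sessions is reached or missed only after allocation, so this set is in effect a looser per-protocol set. A patient with 0 to 6 sessions is outside the primary analysis even if a valid closeout diary is returned.

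Stopping could differ by arm. One arm receives penetrating needles, de qi and current; the other receives neither penetration nor current. Several dropout reasons in section 2.2.3 can depend on treatment or response, and under section 2.3 the investigators receive the group assignment.

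The section 2.7 tests at two-sided 0.05 would inherit any selection. So would the effect size and SD that the Discussion intends to use for sizing the full-scale trial. Since the second set is stricter, no planned analysis would show how much the selection mattered.

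**Working it through.** **1. The plan's own figure.** Section 2.2.4: 18 evaluable per group and 10% dropout. 18 / (1 − 0.10) = 20 per group, 40 in total; this reproduces. Expected dropouts are 0.10 × 20 = 2 per arm, 4 in all. If all stop before session 7, these are the patients the FAS removes.

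**2. Where each patient counts.**

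| Sessions received | FAS (primary) | Per-protocol | Safety |
|---|---|---|---|
| 0 | no | no | no |
| 1–6 | no | no | yes |
| 7–9 | yes, if outcome given | no | yes |
| 10 | yes, if outcome given | yes | yes |

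Last observation carried forward fills gaps only for patients already in a set, so it cannot bring back the first two rows.

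**3. Size of the bias.** The document gives no SD, no effect and no stopping pattern. Assumptions: 20 per arm, no true effect, SD of change 8, and correlation r between the tendency to stop and a poor outcome. If the k patients most prone to stop are removed, that arm's mean looks better by

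r × 8 × S(k) / (20 − k),

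where S(k) is the sum of the k largest expected values among 20 standard normal draws (1.87, 1.41, 1.13). With r = 0.5:

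- k = 1: 4 × 1.87/19 = 0.39
- k = 2: 4 × 3.28/18 = 0.73
- k = 3: 4 × 4.41/17 = 1.04

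The bias in the comparison is the difference between the arms. Rejection rates come from simulation (40,000 replicates, change distributed N(−6, 8) in both arms, two-sample t-test, two-sided 5%). Ranges show variation between runs.

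| Leavers EA / sham | r | Bias by formula (points) | Favours | Rejection |
|---|---|---|---|---|
| 2 / 0 | 0.5 | 0.73 | EA | 6.0–6.1% |
| 3 / 0 | 0.5 | 1.04 | EA | 6.9% |
| 2 / 1 | 0.5 | 0.73 − 0.39 = 0.34 | EA | 5.5–5.7% |
| 2 / 2 | 0.5 | 0 | neither | 5.4–5.5% |
| 1 / 3 | 0.5 | 1.04 − 0.39 = 0.65 | sham | 6.3% |
| 2 / 0 | 1 | 8 × 3.28/18 = 1.46 | EA | 10.0–10.4% |
| 3 / 0 | 1 | 8 × 4.41/17 = 2.08 | EA | 14–14.5% |

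The last two rows are an extreme bound: stopping is decided entirely by outcome, and only in one arm.

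**4. SD carried forward.** With two leavers at r = 0.5, the average sample SD is about 7.6, against about 7.9 with nobody removed. Sample size scales with the SD squared: (7.6/7.9)² = 0.93, so a trial sized on it would be about 7% too small.

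**5. The outcome clause and the imputation rule.** TUFS has one baseline value and one closeout value. Providing the outcome at least once can be met by baseline alone. Carrying that forward gives a change of baseline − baseline = 0. Widening the set without changing this rule would replace selection with imputed zero change wherever V13 is missing.

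**The case against.** The strongest reply is that the effect is likely to be small. The course lasts 18 days, patients are blinded with the same guide tubes and the apparatus switched on in both arms, and this is a pilot with no powered hypothesis. If stopping is unrelated to outcome, or acts alike in both arms with no true effect, the bias is about 0. All of that stands, and it limits severity. It does not justify the definition, which makes an adherence-selected set primary.

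Four stronger readings are tempting and are not supported.

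- *The exclusion favours electroacupuncture.* Unimproved sham patients may stop more often, and the bias then runs the other way (1 versus 3 leavers above).
- *The plan's own 10% dropout implies 10 to 14.5% false positives.* Those rates need 2 or 3 leavers in one arm only, with stopping fully determined by outcome. Two leavers in each arm at correlation 0.5 give about 5.5%. The 10% in section 2.2.4 also covers all dropout, not only stopping before session 7, and three leavers would be 3/20 = 15% of an arm.
- *Retention carried into the next trial would describe adherers only.* Retention is counted from the 40 randomised and does not depend on the FAS.
- *Section 2.2.3 ends data collection for dropped patients.* It lists reasons for dropout and is silent on later outcome assessment. In a condensed article that silence is not an error.

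**Conclusion.** The point holds. Section 2.7 labels as full, and makes primary, a set conditioned on receiving at least 7 of 10 post-allocation sessions, with no all-randomised effectiveness analysis stated beside it. The comparison can be biased in either direction if early stopping relates to outcome differently in the two arms.

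Under the stated assumptions (SD 8, correlation 0.5), the bias ranges from about 1.0 point in favour of electroacupuncture, through 0, to about 0.6 points against it, with rejection of roughly 5.5 to 7% at nominal 5%. The SD for planning is somewhat understated. These figures illustrate a range and do not estimate what will happen; who stops, and why, cannot be known from the document. For an unpowered pilot this is a should-fix.

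**What to change.** In section 2.7:

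- Define the primary effectiveness set as all randomised participants, analysed in the arm allocated, whatever the number of sessions received.
- Keep the set with 7 or more sessions as a supportive or per-protocol analysis; the 10-session set can remain beside it.
- Replace the at-least-once outcome clause and last observation carried forward with an analysis of observed V13 values, for example baseline-adjusted ANCOVA, plus a sensitivity analysis for missing V13 data. A baseline value carried forward should not count as an observed outcome.

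In section 2.2.3, add that participants who stop sessions are still asked for the V13 TUFS diary and questionnaires unless they withdraw consent for data.

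Cost: a few sentences, some effort to obtain V13 diaries from those who stop, and a possibly more diluted estimate. The randomised number stays at 40.
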